# Evaluating Cordyceps militaris capsules on post-bronchodilator FEV_1_ decline in patients with COPD: a study protocol for double-blind, randomized, placebo-controlled trial

**DOI:** 10.3389/fphar.2026.1775068

**Published:** 2026-05-25

**Keywords:** chronic obstructive pulmonary disease, Cordyceps militaris capsules, lung function, post-bronchodilator FEV1, protocol

## Abstract

**Background:**

Chronic Obstructive Pulmonary Disease (COPD) is characterized by a progressive deterioration of lung function, which occurs at its fastest rate in the early stages (GOLD I-II). Preliminary clinical investigation has suggested that *Cordyceps militaris* capsules can improve post-bronchodilator forced expiratory volume in 1 s (FEV_1_) in mild-to-moderate COPD. However, previous studies were limited by the absence of placebo control. Therefore, this trial is designed to evaluate the efficacy and safety of *Cordyceps militaris* capsules versus placebo in improving post-bronchodilator FEV_1_ in patients with mild-to-moderate stable COPD.

**Methods:**

This study is a multi-center, randomized, double-blind, placebo-controlled clinical trial involving 160 eligible patients aged between 40 and 85 years. After a 1-week run-in period, participants are randomized in a 1:1 ratio to receive either *Cordyceps militaris* capsules or placebo capsules for 24 weeks, and are followed for an additional 24 weeks. The primary outcome measure is the change in post-bronchodilator FEV_1_. Secondary outcome measures comprise additional lung function parameters, such as pre-bronchodilator FEV_1_, pre- and post-bronchodilator measures of forced vital capacity (FVC), FEV_1_/FVC ratio, mid-expiratory flow (MMEF), forced expiratory flow 75% (FEF75), forced expiratory flow 50% (FEF50). In addition, frequency of acute exacerbations, time to the first acute exacerbation, COPD Assessment Test (CAT), Cough and Sputum Assessment Questionnaire (CASA-Q), EuroQol five-dimension five-level questionnaire (EQ-5D-5L), and Modified Medical Research Council dyspnea scale (mMRC) are also included.

**Discussion:**

This study is designed to evaluate the therapeutic potential of *Cordyceps militaris* capsules and to provide a traditional Chinese medicine intervention for preserving lung function in mild-to-moderate stable COPD.

**Clinical Trial Registration:**

https://www.chictr.org.cn/, ChiCTR2400086743, identifier, ChiCTR2400086743.

## Introduction

1

Chronic obstructive pulmonary disease (COPD) is a heterogeneous pulmonary disorder primarily caused by structural abnormalities in the airways and/or alveoli. These pathological changes lead to impaired gas exchange and persistent airflow obstruction, which typically worsen over time and is only partially reversible, thereby distinguishing COPD from other obstructive lung diseases (Global Initiative for Chronic Obstructive Lung Disease, 2025; Chronic Obstructive Pulmonary Disease Group of Chinese Thoracic Society and Chronic Obstructive Pulmonary Disease Committee of Chinese Association of Chest Physicians, 2021). Globally, COPD affected an estimated 212.3 million people, and was responsible for 3.3 million deaths and 74.4 million disability-adjusted life years (Collaborators, 2020; Safiri et al., 2022). Given the aging population and growing number of smokers, the prevalence of COPD is expected to increase further, exacerbating its already substantial social and economic burdens (De Oca et al., 2025). Consequently, the challenges associated with the prevention and control of COPD are becoming increasingly severe.

An accelerated decline in lung function, particularly forced expiratory volume in one second (FEV_1_), is a primary risk factor for chronic respiratory diseases. This decline is most commonly caused by smoking in adulthood (Zhang et al., 2024). The Global Initiative for Chronic Obstructive Lung Disease (GOLD) categorizes the severity of COPD into four grades based on the post-bronchodilator FEV_1_ percent predicted (FEV_1_%pred). Studies have demonstrated that mild-to-moderate COPD (GOLD I-II), accounting for approximately 92.7% of all cases, frequently presents with minimal or mild symptoms (Zhou et al., 2017; Lee et al., 2016). However, this phase is paradoxically characterized by rapid deterioration of lung function, with patients experiencing an annual FEV_1_ decline of 49-60 mL/year (Callejas et al., 2016). By the time overt symptoms such as dyspnea and respiratory distress emerge, patients have typically sustained substantial and often irreversible lung damage (Hurst et al., 2021; Barrecheguren et al., 2018). However, long-term pharmacological intervention can improve respiratory outcomes in patients with mild-to-moderate COPD (Wu et al., 2025).

Current pharmacological interventions for improving lung function in COPD remain limited, with Western medicine predominantly focusing on inhaled therapies. A clinical trial has demonstrated that tiotropium bromide can attenuate the annual rate of FEV_1_ decline by 22 mL/year in mild-to-moderate COPD (Zhou et al., 2017). However, GOLD refrains from recommending any specific pharmacological regimen for mild-to-moderate COPD, citing insufficient clinical evidence (Global Initiative for Chronic Obstructive Lung Disease, 2025). Therefore, there is an urgent need for more rigorous clinical trials to establish evidence-based therapeutic regimens for managing mild-to-moderate COPD.

*Ophiocordyceps sinensis* (Berk.) G.H. Sung et al. (syn. *Cordyceps sinensis*) is a highly valued medicinal fungus in Traditional Chinese Medicine (TCM) (Wang et al., 2016). A meta-analysis has demonstrated that the adjunctive use of *Cordyceps sinensis* prescription with conventional Western medicine can significantly improve lung function parameters, particularly FEV_1_%pred and forced expiratory volume in 1 s/forced vital capacity (FEV_1_/FVC) ratio, in patients with COPD (Yu et al., 2019). At the molecular level, Zhou et al. revealed that *Cordyceps sinensis* regulates glycerophospholipid and sphingolipid metabolism by targeting PLA2G4E and B4GALT4 proteins via the PI3K-AKT pathway. This mechanism may underlie its anti-inflammatory and lung-protective effects against COPD (Zhou et al., 2025). However, the rarity and high cost of wild *Cordyceps sinensis* have driven the development of industrialized fermentation techniques for *Cordyceps militaris* (L.) Fr. 1818 production. This cultivated species contains analogous bioactive compounds and represents a sustainable, clinically viable alternative for medicinal applications (Das et al., 2010).

Modern pharmacological studies have identified multiple bioactive compounds in *Cordyceps militaris*, including cordycepin, polysaccharides, ergosterol, and mannitol, which exhibit various physiological effects such as immunomodulation, antibacterial and anti-inflammatory activity, and antitumor properties (Olatunji et al., 2018). In a multicenter randomized controlled trial, treatment with *Cordyceps militaris* capsules for 24 weeks increased FEV_1_ by 140 mL in mild-to-severe COPD patients, compared to a 10 mL decrease in the Bailing capsule group (Li et al., 2025). Notably, in the mild-to-moderate COPD subgroup, *Cordyceps militaris* capsules improved post-bronchodilator FEV_1_ by 86 mL versus a 41 mL decline in the control group (*P* < 0.05). Although the study lacked placebo control and used acute exacerbation events as the primary endpoint, the findings remain promising.

Therefore, this study is designed as a multi-center, double-blind, placebo-controlled randomized trial to evaluate the efficacy of *Cordyceps militaris* capsules versus placebo in improving post-bronchodilator FEV_1_ in mild-to-moderate COPD, and will provide evidence for a TCM intervention for preserving lung function in patients with mild-to-moderate COPD.

## Methods and analysis

2

### Investigational medications

2.1

All investigational medications, including both the *Cordyceps militaris* capsules and placebo capsules, have been manufactured by Jilin Zhongsheng Pharmaceutical Co., Ltd.

*Cordyceps militaris* capsules (National Drug Approval Number: Z20030035) are the cultured form of *Cordyceps militaris* (L.) Fr. 1818, a species belonging to the genus *Cordyceps* and the family Clavicipitaceae*.* The *Cordyceps militaris* strain is inoculated onto oak silkworm pupae and cultured at 15 °C-22 °C for approximately 45 days. After the stroma has grown, the material is harvested, dried at 60 °C and ground into a fine powder. After the addition of excipients through subsequent processing steps, the final capsules are produced. The detailed preparation of *Cordyceps militaris* capsules is shown in Supplementary Material 1. Jilin Zhongsheng Pharmaceutical Co., Ltd. has conducted constituent analysis and quality control testing through high-performance liquid chromatography and gas chromatography. The voucher specimens have been stored in the company warehouse. The composition analysis of *Cordyceps militaris* capsules and quality-control fingerprints are shown in Supplementary Material 2. In addition, a drug testing report for *Cordyceps militaris* capsules with detailed information is provided in Supplementary Material 3. No significant adverse reactions have been reported in previous clinical studies, suggesting a favorable safety profile (Li et al., 2025).

The main components of the placebo capsules are dextrin, corn starch, caramel, tartrazine, lentinus edodes (shiitake) powder, and dried flatfish powder. The placebo capsules match *Cordyceps militaris* capsules in smell, appearance, taste, and weight, thereby ensuring effective blinding. The preparation is shown in Supplementary Material 1, and drug testing reports are shown in Supplementary Material 4.

### Study design

2.2

This is a multi-center, randomized, double-blind, parallel-group, placebo-controlled clinical trial. The trial has been initiated by the Guangdong Provincial Hospital of Chinese Medicine. After a 1-week run-in period, a total of 160 eligible participants are randomized to the treatment group (*Cordyceps militaris* capsules) or the control group (placebo capsules) in a 1:1 ratio. Participants receive a 24-week intervention and an additional 24-week follow-up period. Study visits will take place at baseline and weeks 12, 24, 36, and 48 within 30 days of each scheduled visit. Participants are required to provide written informed consent. The protocol follows the principles of the Standard Protocol Items: Recommendations for Interventional Trials (SPIRIT) Guidelines. A flowchart of the trial is shown in Figure 1. The schedule of enrollment, interventions, and assessments is presented in Table 1.

**FIGURE 1 F1:**
[figure not shown]
Study flow chart. COPD, Chronic Obstructive Pulmonary Disease; CAT, COPD Assessment Test; CASA-Q, Cough and Sputum Assessment Questionnaire; EQ-5D-5L, EuroQol five-dimension five-level questionnaire; mMRC, Modified Medical Research Council dyspnea scale.

**TABLE 1 T1:** A standard protocol items: recommendations for interventional trials (SPIRIT).

Trial period						
Timepoint	Enrollment		Post randomization			Close out
	-t_1_-0 −1 week	0 0 weeks	t_1_ 12 weeks	t_2_ 24 weeks	t_3_ 36 weeks	t_4_ 48 weeks
Enrollment						
Eligibility screen	×	​	​	​	​	​
Informed consent	×	​	​	​	​	​
Demographic data	×	​	​	​	​	​
Medical history	×	​	​	​	​	​
Allergic history	×	​	​	​	​	​
Randomization	​	×	​	​	​	​
Intervention or comparator						
Intervention	​	×		×	​	​
Comparator	​	×		×	​	​
Assessments						
Lung function	(×)	×	×	×	×	×
CAT	​	×	×	×	×	×
CASA-Q	​	×	×	×	×	×
mMRC	​	×	×	×	×	×
EQ-5D-5L	​	×	×	×	×	×
Assessment of acute exacerbation	×	×	×	×	×	×
General physical examination	×	×	×	×	​	​
Blood routine	×	​	×	×	​	​
Liver and kidney function	×	​	×	×	​	​
AEs	​	×	×	×	×	×
Others						
Biological samples	​	×	​	×	​	×
Distribution of drugs	​	×	×	​	​	​
Recycling of drugs	​	​	×	×	​	​
Completion of CRF	×	×	×	×	×	×
Summary of study conclusion	​	​	​	​	​	×

### Participants

2.3

#### Recruitment and trial setting

2.3.1

Participants are recruited from multiple hospitals across China. These participating centers include Guangdong Provincial Hospital of Chinese Medicine, the First Affiliated Hospital of Guangzhou University of Chinese Medicine, the Second People’s Hospital of Baiyun and Guangzhou, Nanfang Hospital Southern Medical University, China-Japan Friendship Hospital and Jiangxi Provincial Hospital of Chinese Medicine. Participants are screened and assessed primarily in outpatient clinical settings by researchers. Additionally, recruitment advertisements may also be used to identify eligible patients. Only patients who meet all the inclusion criteria and none of the exclusion criteria will be enrolled. Enrolled participants undergo treatment and follow-up in strict accordance with the study protocol. The study commenced on 9 July 2024. Patient recruitment is expected to be completed by late 2026, and the entire trial is projected to conclude by late 2027.

Detailed baseline characteristics are collected for all enrolled participants, including sex, age, medical history, allergy history, disease duration, concomitant medications, smoking status (current, former, or never smoker), smoking index, and duration of smoking cessation.

#### Diagnostic criteria of diseases

2.3.2

GOLD 2024 (Global Initiative for Chronic Obstructive Lung Disease, 2024) is used for the diagnosis of COPD, grading of pulmonary function, and disease staging.1. Western medicine diagnostic criteria for COPD:① Symptoms: Dyspnea, and/or chronic cough and sputum;② Risk factors: Smoking, exposure to smoke from cooking and heating fuels, exposure to occupational dust and chemicals, or a family history of COPD;③ Lung function: Post-bronchodilator FEV_1_/FVC <70%;④ Exclusion: Other airflow restricted diseases causing similar symptoms, such as asthma, bronchiectasis.2. Grading of lung function

GOLD I: Post-bronchodilator FEV_1_/FVC <70% and post-bronchodilator FEV_1_%pred ≥80%.

GOLD II: Post-bronchodilator FEV_1_/FVC <70% and 50% ≤ post-bronchodilator FEV_1_%pred <80%.3. Staging of COPD

Stable stage: Cough, sputum, and dyspnea are stable or mild, and the patient has returned to baseline status prior to acute exacerbation.

Acute exacerbation: An event characterized by worsening dyspnea and/or worsening cough and sputum over a period of less than 14 days (a sudden deterioration of respiratory symptoms beyond the usual variation) (Global Initiative for Chronic Obstructive Lung Disease, 2024). The cardinal symptom is worsening dyspnea, typically accompanied by wheezing, chest tightness, increased cough frequency, increased sputum volume, altered sputum characteristics (e.g., color and/or viscosity), and fever.4. Acute exacerbation severity is classified as:

Mild: Treated with short-acting bronchodilators only.

Moderate: Treated with short-acting bronchodilators and antibiotics, with or without oral glucocorticoids.

Severe: requiring hospitalization, emergency department treatment or intensive care unit admission.

#### Diagnostic criteria of syndrome of lung qi deficiency

2.3.3

Lung qi deficiency syndrome is diagnosed according to Guidelines of integrated Chinese and western medicine for diagnosis and treatment of chronic obstructive pulmonary disease (2022) (Li et al., 2023).Cough or wheezing, shortness of breath, which aggravated while moving;Mental fatigue, lack of strength, or spontaneous sweating;Aversion to wind, easy to catch cold;Light tongue with white coating.

The syndrome can be diagnosed when meeting three items of the above ①–④.

#### Inclusion criteria

2.3.4

Participants who meet the following criteria are included:Aged 40-85 years;Diagnosed with COPD according to the criteria of the GOLD 2024 and Guidelines for the Diagnosis and Management of Chronic Obstructive Pulmonary Disease (Revised Version 2021), with lung function classified as GOLD I-II;Stable COPD, with no respiratory infections or acute exacerbations of COPD within 4 weeks before screening;With the TCM syndrome of lung qi deficiency;Informed and signed the informed consent form.

#### Exclusion criteria

2.3.5

Participants with any of the following conditions are excluded.With bronchiectasis, asthma, malignant lung tumor, active pulmonary tuberculosis etc.,With an acute exacerbation of COPD at screening or within 4 weeks before screening;Inability to cooperate with pulmonary function testing;With long-term use of traditional Chinese medicine diet such as astragalus, ginseng, Codonopsis;With severe cardiovascular, cerebrovascular, liver or kidney diseases, mental disorders;With abnormal liver function [ALT or AST ≥2 times the upper limit of normal (ULN)] or abnormal kidney function (serum creatinine ≥2 times ULN);Patients with a history of allergy or hypersensitivity reaction to the investigational product or its components, or patients believed by the investigator to have diseases that should prohibit the use of the investigational drug;Patients who are participating in or planning to participate in, other clinical trials with 1 month before screening or during the observation period;Deemed ineligible for the study by the investigator.

#### Withdrawal/termination criteria

2.3.6

Participants are withdrawn from the trial if they meet any of the following criteria.Serious adverse events (SAEs) related to the investigational treatment occur.Serious complications, allergic reactions, clinically significant liver or kidney dysfunction, significant physiological changes that occur during the trial.Continued participation poses unacceptable risks to the participant, as judged by the principal investigator.Participants who experience recurrent infections during treatment will be withdrawn under the automatic withdrawal criteria. Specifically, if a participant experiences two or more acute exacerbations within 1 month requiring emergency department visits or hospitalization, the participant will be automatically withdrawn from the study to mitigate the risk of clinical deterioration and safeguard participant welfare.

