### Outcomes and measurements

2.8

The time points of the study data collection for outcome measurements are shown in Table 1.

The primary outcome is change in the post-bronchodilator FEV_1_. Lung function assessments are performed once each at baseline, weeks 12, 24, 36, and 48. Secondary outcomes include additional lung function parameters, such as pre-bronchodilator FEV_1_, pre- and post-bronchodilator measures of FVC, FEV_1_/FVC ratio, mid-expiratory flow (MMEF), forced expiratory flow 75% (FEF75) and forced expiratory flow 50% (FEF50). In addition, frequency of acute exacerbations, time to the first acute exacerbation, COPD Assessment Test (CAT), Cough and Sputum Assessment Questionnaire (CASA-Q), EuroQol five-dimension five-level questionnaire (EQ-5D-5L), and Modified Medical Research Council dyspnea scale (mMRC) are also included. These outcomes are also measured once each at baseline, weeks 12, 24, 36 and 48.

Blood, sputum and stool samples are collected from at least 60 participants enrolled in the Guangzhou center for metagenomics (airway and intestinal flora), transcriptomics, metabolomics, proteomics analyses and induced sputum cell classification. Biological samples are collected at baseline, weeks 24 and 48 after treatment, following standard operating procedures for acquisition, processing, and cryopreservation.

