### Statistical analysis

2.11

The analysis will be performed using the intention-to-treat principle on the full analysis set, with additional analyses conducted on the per-protocol set and safety set. Only authorized study personnel will be able to view and manage data. The between-group comparison of acute exacerbation frequency will be conducted using a Poisson regression model that includes treatment group as the independent variable, annualized exacerbation rate as the dependent variable, and stratified randomization factors as adjustment covariates. Least squares means with corresponding 95% confidence intervals (with appropriate transformations when required) will be estimated from the specified model to evaluate between-group differences. Continuous variables will be analyzed using appropriate parametric (two-sample t-test or adjusted t-test) or nonparametric (Wilcoxon rank-sum test) methods, while categorical variables will be evaluated using either Pearson’s chi-square test or Fisher’s exact test. Time-to-event endpoints will be analyzed using Kaplan-Meier methodology, with median event times and interquartile ranges (IQR, 25th-75th percentiles) estimated for each group. Between-group differences will be assessed using log-rank tests. For missing data, the last observation carried forward method will be employed for imputation. For the center effect analysis, continuous variables will be analyzed using analysis of covariance or meta-analysis, while categorical variables will be assessed using Cochran-Mantel-Haenszel statistics.

Baseline demographic and clinical characteristics, including age, sex, disease duration, smoking status, smoking index, medical history, and concomitant medications, will be summarized descriptively and assessed for balance between groups. When appropriate, adjusted analyses will be conducted by including these variables as covariates in multivariable models to reduce the impact of potential confounding factors on treatment effect estimation. In addition, prespecified subgroup analyses stratified by sex will be performed to explore potential differences in treatment response to *Cordyceps militaris* capsules.

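### Withdrawal criteria remove participants from the trial rather than from study drug, and one automatic trigger is itself part of a secondary outcome

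*Protocol article*

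**What the plan says.** Section 2.3.6 opens with "Participants are withdrawn from the trial if they meet any of the following criteria". Its list covers treatment-related serious adverse events, serious complications, allergic reactions, significant liver or kidney dysfunction, significant physiological changes, and unacceptable risk as judged by the principal investigator. It then adds a rule for the treatment period that leaves no discretion: "if a participant experiences two or more acute exacerbations within 1 month requiring emergency department visits or hospitalization", then "the participant will be automatically withdrawn from the study to mitigate the risk of clinical deterioration and safeguard participant welfare".

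Four other sections bear on this:

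- Section 2.3.2 grades exacerbations. Its top grade reads "Severe: requiring hospitalization, emergency department treatment or intensive care unit admission", which covers the events in the automatic rule.
- Section 2.8 lists "frequency of acute exacerbations, time to the first acute exacerbation" among the secondary outcomes. For the primary outcome it says "Lung function assessments are performed once each at baseline, weeks 12, 24, 36, and 48", with no condition that the participant is still on drug and no mention of withdrawn participants.
- Section 2.11 says "The analysis will be performed using the intention-to-treat principle on the full analysis set" and fills missing data by last observation carried forward (LOCF). Exacerbation frequency is to be compared by a Poisson model "that includes treatment group as the independent variable, annualized exacerbation rate as the dependent variable".
- Section 2.14 allows study medication to be stopped after severe or clinically significant treatment-related events, or where the investigator sees unacceptable risk. Beyond that it provides only for safety follow-up of the event.

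**The concern.** Stopping a drug and leaving a trial are different things. An intention-to-treat comparison needs outcomes from everyone randomized, including those who stop treatment because they do badly. Section 2.3.6 ends participation for events that occur after randomization, may differ between arms, and are tied to the disease course. For the automatic rule the tie is direct, because the trigger is a run of secondary-outcome events.

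If scheduled visits end at that point, two things follow. Later FEV1 values are replaced by the last one seen. A participant withdrawn before the first post-baseline spirometry at week 12 has only the baseline to carry forward, so the change is set to zero. In addition, exacerbation follow-up is cut short because of events, so the observed rate for that person is high. If more placebo patients meet the rule, the first effect works against the drug, since unseen losses on placebo are hidden. The second can overstate a benefit on exacerbations. Time to first exacerbation is not lost through the automatic rule, because the first event has already happened.

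Sections 2.3.6 and 2.14 also give different instructions where they overlap. For unacceptable risk, and for related serious events that are also severe or clinically significant, one requires leaving the trial and the other offers an optional stop of medication.

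**Working it through.** The article gives no figure for how many participants will meet these criteria. The 15% attrition allowance in section 2.6 is not broken down by cause. The sizes below are therefore illustrations, with assumptions marked.

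**FEV1**

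Inputs: SDs of 250 and 201 mL, a difference of 110 mL and 80 per arm (section 2.6); decline of 49 to 60 mL/year in mild-to-moderate disease (section 1). Assumed: 2 to 5 percentage points more of one arm withdrawn (0.02 × 80 = 1.6 to 0.05 × 80 = 4 patients), and an unseen loss equal to that decline over the full 48 weeks.

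- SE of the difference = √(250²/80 + 201²/80) = 35.9 mL
- Unseen loss = 49 × 48/52 = 45.2 mL to 60 × 48/52 = 55.4 mL
- Bias = 0.02 × 45.2 = 0.90 mL to 0.05 × 55.4 = 2.77 mL
- Relative to 110 mL: 0.8% to 2.5%. Relative to the SE: 0.03 to 0.08

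Patients with repeated severe exacerbations may lose more than the average decline, but the article gives no figure for that.

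**Exacerbation rate, each patient's annualized rate as the response**

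Take one patient with two events who is withdrawn under the automatic rule, and compare with the same patient followed to week 48 with no further event: 2/(48/52) = 2.17 per year. The rule applies during treatment, so withdrawal falls by about week 24 and about half or more of the 48 weeks is lost. The arm rates of 1.0 and 0.5 per year are assumed.

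| Withdrawn at week | Rate per year | Shift in mean of 80 | % of 1.0/year | % of 0.5/year |
|---|---|---|---|---|
| 8 | 2/(8/52) = 13.0 | (13.0 − 2.17)/80 = 0.135 | 13.5 | 27.1 |
| 12 | 2/(12/52) = 8.67 | (8.67 − 2.17)/80 = 0.081 | 8.1 | 16.3 |
| 24 | 2/(24/52) = 4.33 | (4.33 − 2.17)/80 = 0.027 | 2.7 | 5.4 |

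**Exacerbation rate, counts with follow-up time as offset**

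- Full exposure in one arm = 80 × 48/52 = 73.85 person-years
- Lost by one withdrawal at week 8 = 40/52 = 0.77, leaving 73.08
- No later events missed: 73.85/73.08 = 1.0105, or +1.1%
- Two later events unrecorded, arm rate 1.0: (73.85 − 2)/73.08 = 0.983, or −1.7%
- Two later events unrecorded, arm rate 0.5: (36.92 − 2)/73.08/0.5 = 0.956, or −4.4%

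The effect on the exacerbation comparison therefore depends heavily on how the model is fitted, and under the offset form its sign depends on what happens after withdrawal.

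**The case against.** The strongest reply is that the harm is inferred. The article never says visits cease, and handling of withdrawn participants is the kind of detail a full protocol may hold. Section 2.10 aims at retention and complete follow-up. Section 2.7 keeps participants on drug through an exacerbation where possible, so mild, moderate, isolated severe and well-separated severe events do not trigger the automatic rule. In GOLD I-II patients who are stable at entry, a cluster of emergency or hospital events in one month should be rare.

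On size, the FEV1 bias is trivial. If the change is read at week 24, at most 24 weeks go unseen (22.6 to 27.7 mL), and the bias falls to about 0.5 to 1.4 mL, or 0.01 to 0.04 of the SE. The 14 to 27% figure needs early withdrawal, no later events and a model of unweighted individual rates. A conventional Poisson fit with an offset removes most of it. Nothing in the article shows that placebo patients would trigger the rule more often.

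Much of this stands: few patients are likely to be affected, the primary result barely moves, and the direction is not established. It does not remove the point. The article states a positive rule in terms of the trial and the study, which is more than silence. The retention text in section 2.10 concerns telephone scheduling and reminders, not people already withdrawn. Section 2.7 leaves the automatic rule untouched. And the model as written in section 2.11 names the annualized rate, not the count, as the response.

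**Conclusion.** The point holds, as a change that should be made rather than a flaw that threatens the primary result. As written, section 2.3.6 ends trial participation because of outcome-related events, which conflicts with the stated analysis principle and loses data that could be collected. That scheduled visits stop is an inference from the wording and from the safety-only follow-up in section 2.14. Confidence is medium for that reason.

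The effect on FEV1 is negligible under the assumptions used. Exacerbation frequency is the exposed outcome: a single early withdrawal can matter if individual annualized rates are modelled, and matters little if counts with an offset are used. Both sizes rest on assumed arm rates and withdrawal times, since the article gives neither.

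**What to change.** Reword section 2.3.6 so that its criteria are reasons to stop study drug, with the clinical thresholds unchanged, and use the same action in section 2.14. State that scheduled spirometry, exacerbation and adverse event assessments continue to week 48 unless the participant withdraws consent or the visit itself would be unsafe. State also that these data are included in the full analysis set.

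Participant protection is not reduced: the drug still stops at the same point, and exacerbations are still managed by guidelines under section 2.7. All participants are already scheduled for off-drug visits at weeks 36 and 48, so the follow-up structure exists. The cost is a protocol amendment with ethics review in a multicentre trial that has been running since July 2024, plus a few already scheduled visits for participants off drug. Recruitment is expected to run to late 2026, so participants still to enrol or in follow-up when the amendment takes effect would benefit.
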